##### Core temperature

2.4.6.3

Tcore will be evaluated through the entire trial through a telemetric pill ingested 60 min prior the start of the session (BodyCap®, Hérouville-Saint-Clair, France). Due to the good measuring accuracy, the ability to measure in field-based situations and the non-invasive character of this temperature measurement method, the ingestible telemetric temperature pill is suitable to assess Tcore during exercise [38].

##### Physical performance

2.4.6.4

Physical performance responses will be measured using 100 Hz accelerometery, with Sonda 4.0 software (StatSports®, London, UK) to estimate total distance, sprint distance, accelerations, and decelerations.

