#### Exercise protocol

2.4.4

The SAFT90 protocol emulates the intermittent and multi-directional nature of football match-play, with frequent changes in direction and activity [32]. It is based on time-motion analysis data from the English Championship level match play acquired during the 2007 season [31], and simulates the activity demands and physiological responses of football match play [33]. Players navigate around a 20 m agility course in an intermittent fashion via standing (0 km h^−1^), walking (5.5 km h^−1^), jogging (10.7 km h^−1^), striding (15.0 km h^−1^) or sprinting (maximal effort). The players cover 11.1 km in total, 18.5% of this distance (2.04 km) is performed at high-speed (≥15 km h^−1^) with 1269 changes in speed (every 4.3 s), and 888 changes in direction (180°) and 444 cutting manoeuvres over the 90 min (1332 directional changes). The protocol is divided into equivalent 15-min activity profiles, lasts 90 min and is performed on an indoor running surface. The type of movement activity and intensity is controlled using verbal signals from an audio MP3 file [31].

The participants of the present study will perform a standardized pre-match routine in terms of rest, nutrition, hydration and physical preparation and a 15-min warm-up will precede the 90-min simulation, which is going to be interceded by a 15-min passive half-time interval.

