#### Outcomes

2.4.6

The primary outcomes of interest for this study involve physiological, physical and perceptual parameters. Physiological primary outcomes include heart rate (HR), SR and Tcore.

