**T19**	The second 15-min block of the first half will begin.
**T20**	TC, PT and TS will be evaluated after the end of the second block.
**T21**	First “water break” is now going to occur. The third 15-min block of the first half will start.
**T22**	TC, PT and TS will be assessed after the end of the third block and half-time period is going to start.
**T23**	If needed, participants will towel-dry themselves and then have their body mass measured (before and after urine excretion) with the same scale and while wearing the same clothes as the pre-exercise body mass assessment. Water bottles will be weighted.
**T24**	The same beverage (as in T8) will be provided to each participant, exactly in same conditions as in the pre-cooling phase. The first 1/3 of the 75 ml of the same beverage will be administered.
**T25**	TC, PT and TS will be recorded.
**T26**	The second 1/3 of the 75 ml of per-cooling beverage will be distributed.
**T27**	TC, PT and TS will be evaluated.
**T28**	The third 1/3 of the 75 ml of per-cooling beverage will be administered.
**T29**	TC, PT and TS will be accessed.
**T30**	The first 15-min block of the second half will start.
**T31**	TC, PT and TS will be recorded again after the end of the fourth block.
**T32**	The second 15-min block of the second half will begin.
**T33**	TC, PT and TS will be evaluated after the end of the fifth block.
**T34**	Second “water break” will occur. The third 15-min block of the second half will start.
**T35**	TC, PT and TS will be evaluated at the end of the sixth block.
**T36**	Lactate and blood glucose levels are going to be reassessed.
**T37**	Participants will towel-dry themselves and then have their body mass measured (before urine excretion) with the same scale and while wearing the same clothes as the pre-exercise body mass assessment. Water bottles will be weighed. Subsequently, the difference between the referee's weight at T4 and T37 is going to be calculated, to estimate whole-body sweat loss as well as SR during the protocol (the volume of fluid intake is going to be subtracted, as well as urine output).
**T38**	Hydration status is going to be evaluated, after urine collection.
**T39**	RPE will be assessed.

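### Total distance, and to a lesser extent accelerations and decelerations, are largely set by the audio-paced SAFT90, so they are weak primary measures of a performance decrement

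*Protocol article*

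**What the plan says.** All references are to the protocol article.

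- **Outcomes (2.4.6):** "The primary outcomes of interest for this study involve physiological, physical and perceptual parameters". Section 2.4.6.4 lists the physical ones: the accelerometer is used "to estimate total distance, sprint distance, accelerations, and decelerations".
- **Exercise protocol (2.4.4):** the SAFT90 is run on a 20 m course in equivalent 15-min profiles. Walking, jogging and striding have set speeds (5.5, 10.7 and 15.0 km/h), and only sprinting is at maximal effort. Pacing is external: "The type of movement activity and intensity is controlled using verbal signals from an audio MP3 file". The workload is given as "The players cover 11.1 km in total, 18.5% of this distance (2.04 km) is performed at high-speed", with "1269 changes in speed (every 4.3 s") and "888 changes in direction (180°) and 444 cutting manoeuvres over the 90 min (1332 directional changes").
- **Aim:** the Abstract wants to learn whether menthol attenuates performance decrements, and the Discussion expects a performance benefit.
- **Statistics (2.7):** accelerometry data are among the responses tested for an association with the intervention. Participants who discontinue or deviate from intervention protocols are excluded.
- **Table 1 (2.4.7):** thermal comfort (TC), perceived thirst (PT) and thermal sensation (TS) are rated repeatedly through the session. RPE has a single entry, at T39: "RPE will be assessed".

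**The concern.** An outcome can show a treatment effect only if participants are free to score differently on it. Here the exercise prescribes much of what the physical outcomes record. If both sessions are run to the same track, distance covered is close to a design constant, and the number and timing of speed changes are scripted.

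The risk lies in interpretation. The trial asks a performance question, and the supporting studies cited in the Discussion used time to exhaustion, power output and time-trial completion, all of which can vary freely. Similar distances under menthol and placebo would be the expected finding whether or not menthol helps, yet could be reported as absence of an ergogenic effect. The limitations paragraph says that SAFT90 is not validated for referees but does not mention that the external load is prescribed.

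**Working it through.** **1. Do the workload figures describe one fixed script?** Inputs are from section 2.4.4.

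- High-speed distance: 0.185 × 11.1 km = 2.05 km. The stated figure is 2.04 km, and 2.04 / 11.1 = 18.4%, so the two agree to rounding.
- Interval between speed changes: 90 × 60 s / 1269 = 5400 / 1269 = 4.26 s, stated as 4.3 s.
- Directional changes: 888 + 444 = 1332, as stated.

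The figures are consistent with each other and describe a prescribed load that is the same for both conditions.

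**2. How much of the distance is free to vary?**

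- Distance below 15 km/h: 11.1 − 2.04 = 9.06 km, and 9.06 / 11.1 = 82%. All of it is at paced speeds.
- The remaining 2.04 km includes striding at 15.0 km/h, which is also paced. Sprinting is therefore at most 2.04 km; the article does not give its share.
- Dilution: if high-speed distance changes by a fraction r and the rest is run as paced, total distance changes by r × 2.04 / 11.1 = 0.18 r. Even if all high-speed running could respond, total distance would carry less than a fifth of the relative effect.

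**3. What contrast is expected?** If participants follow the audio, total distance is 11.1 km under menthol and 11.1 km under placebo, so the expected difference is 0 km. A valid test at the 5% level would then be significant about 5% of the time, with 10, 13 or any other number of participants. A larger sample would not help.

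**4. Which listed outcomes are constrained?**

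| Outcome | Set by the track? | Room to respond |
|---|---|---|
| Total distance | Largely | Falling behind the audio |
| Accelerations, decelerations | Number and timing of speed changes scripted | Size, or counts above a threshold, around sprints |
| Sprint distance | When and where sprints occur | Effort within the sprint, depending on how the measure is defined |

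**5. Where else could a benefit appear?** At a largely fixed workload it could show in HR, Tcore, TS, TC or RPE. Counting Table 1:

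- TC, PT and TS are each rated at T7, T9, T11, T13, T16, T18, T20, T22, T25, T27, T29, T31, T33 and T35, which is 14 times.
- Seven of these (T7, T9, T11, T13, T25, T27, T29) are at rest around the rinses, where exertion is not at issue. One (T16) follows the warm-up. Six (T18, T20, T22, T31, T33, T35) close the exercise blocks.
- RPE is rated once, at T39, after blood sampling (T36), towelling and weighing (T37) and urine collection (T38).

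The fair comparison for RPE is therefore 1 rating against 6 end-of-block ratings.

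**The case against.** A reader might infer that these outcomes cannot show any effect and that a null result is close to guaranteed. The article does not support that, for four reasons.

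- **Cues do not enforce speed.** Verbal signals guide a runner on a floor. The 11.1 km describes the SAFT90, built from players' match data, and nothing says that every referee will achieve it in the planned heat. Falling behind would lower distance. This stands, so the zero difference in step 3 is conditional on adherence.
- **The exclusion rule is ambiguous.** One might say that section 2.7 removes anyone who falls behind. It speaks of intervention protocols, and the intervention is the mouth rinse, so slow running need not be covered. Both readings are open, which is a reason to settle the wording.
- **Acceleration measures are undefined in the article.** They may be counts, counts above a threshold, or sizes, and they can vary around maximal sprints. The point is therefore weaker for them than for distance. Leaving such definitions to a fuller document is not itself a fault.
- **Sprint distance is listed and may respond.** If it is distance above a speed threshold (an assumption, since no definition is given), it depends on sprint speed. The performance question is then not wholly unmeasured.

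It is also fair to say that a fixed load suits HR, Tcore and the thermal scales, and that one end-of-session RPE is a recognisable choice. Both are true. They confine the problem to the physical outcomes and make the RPE change an improvement, not a correction of an error.

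**Conclusion.** The point holds in a limited form. Total distance is largely constrained to be equal in the two conditions, and accelerations and decelerations are constrained to a lesser extent. They are weak measures of a performance decrement, and a null result on them should not be read as no ergogenic effect. Sprint distance is the one listed physical outcome tied to the part of the exercise that is free to vary.

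In size: at least 82% of the prescribed distance is at paced speeds, a relative change in high-speed running reaches total distance at about 18% of its size, and the expected difference in distance is 0 km when the audio is followed. This assumes that section 2.4.4 describes the exercise as it will be run and that most referees keep pace. The less they keep pace, the more informative total distance becomes, provided that those who fall behind stay in the analysis. The physiological and thermal outcomes are not affected.

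**What to change.** 1. **Main physical outcome.** Use performance in the maximal-effort sprints, compared between conditions by 15-min block (blocks 1 to 6). Sprint distance is already listed. Add peak or mean sprint speed if the device measures it validly indoors on a 20 m course, which the article does not establish and which should be confirmed first.
2. **Workload check.** Report total distance, accelerations and decelerations mainly to show that both sessions delivered the same work, and state that similarity on them is not evidence against an ergogenic effect.
3. **Exclusion wording.** State in section 2.7 that failing to keep pace with the audio is not a deviation leading to exclusion, so that any decrement seen this way is retained.
4. **RPE.** Rate it with TC, PT and TS at T18, T20, T22, T31, T33 and T35, and add it to the responses listed in section 2.7, where it does not now appear.

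Cost: if the device proves adequate, the sprint measure needs no extra session or equipment. Each added RPE rating takes a few seconds. The downside is that sprint speed may be noisier than distance.

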##### Perceptual parameters

2.4.6.5

Perceptual responses that are going to be evaluated in this study include 4 subjective scales: RPE, TC, perceived thirst (PT) and TS. RPE will be recorded through CR-10 Borg scale [39] that goes from 0 (“rest”) to 10 (“maximal effort”). TC is going to be assessed according to a 6-point scale from to −3 (“very uncomfortable) to 3 (“very comfortable”) [40]. PT will be evaluated recurring to a 7-point scale from 1 (“not thirsty at all”) to 7 (“very, very thirsty”) [27]. TS will be recorded with a 9-point scale (33) from −4 (“very cold”) to 4 (“very warm”) [41].

Secondary outcomes of this study include hydration status, *ad libitum* fluid intake during “water breaks”, lactate, and glucose blood levels.

##### Hydration status

2.4.6.6

Hydration status is going to be assessed through urine specific gravity, recurring to urine test strips (Combur10 Test M, Roche, Switzerland) and a Urisys 1100® analyzer (Roche, Switzerland) before the start and at the end of the session. Hydration status will also be evaluated through urine colour assessment, by a trained researcher, according to Armstrong scale [36].

##### Ad libitum fluid intake

2.4.6.7

*Ad libitum* fluid intake allowed on “water break” time is going to be recorded through the same procedures used to estimate fluid intake as previously described methods to assess SR evaluation.

##### Blood lactate and glucose levels

2.4.6.8

Blood lactate and glucose levels will be measured before and after the protocol, recurring to a Blood Lactate Meter (Lactate Pro 2, Arkray, U.S.A) and a Glucometer (FreeStyle Precision Neo, Abbott Laboratories, U.S.A), respectively. Both devices have been previous validated [42,43].

#### Experimental trial protocol

2.4.7

The protocol of the trial will be divided into 39 phases (T1-T39) (Table 1 and Fig. 1). The participants will arrive at the testing facilities 1 h before the start of the warm-up. Schedule of the enrolment, interventions, and assessments is described in Fig. 2.

**Table 1 tbl1:** Description of the experimental trial phases.

**T1**	BodyCap® will be ingested by the participant.
**T2**	Then, participant's 24-h food recall diary will be collected.
**T3**	Hydration status will be assessed, after urine collection.
**T4**	After voiding their bladder, body mass will be measured on a digital platform scale, weighted with minimal clothing. Individual marked drink bottles will be distributed to the referee so that fluid consumed at “water breaks” may be recorded via the measurement of body mass changes. Participants will be informed that they may drink water *ad libitum*, on “water breaks”.
**T5**	Lactate and blood glucose levels are now going to be measured.
**T6**	Devices for assessing HR and physical performance parameters will now be placed on the referee and synchronized.
**T7**	TC, PT and TS are will be measured.
**T8**	Beverages (previously prepared and stored at the intended temperature) will be distributed to the referee. Total amount of beverages for pre-cooling previously described (75 ml of beverage A or B) will be divided into 3 equal parts and made available to the participant every 1 min. Beverages temperature will be monitored with a digital thermometer, to the nearest 0.1 °C (Proficook, Germany). The entire cooling stage will be carried out at a mild temperature of 18–20 °C, at rest. Participants will be instructed to swill both beverages for 10-s before spitting into a bowl without swallowing. The first 1/3 of the 75 ml of beverage will be administered.
**T9**	TC, PT and TS will be again evaluated.
**T10**	The second 1/3 of the 75 ml of pre-cooling beverage will be distributed.
**T11**	TC, PT and TS will be recorded.
**T12**	The third 1/3 of the 75 ml of pre-cooling beverage will be administered.
**T13**	TC, PT and TS will be again evaluated.
**T14**	Ambient temperature, relative humidity, and heat stress and WBGT will be recorded.
**T15**	Participants will start the 15-min warm-up.
**T16**	After the warm-up, TC, PT and TS will be again evaluated.
**T17**	The first 15-min block of the first half will start.
**T18**	TC, PT and TS will be recorded again after the end of the first block.
**T19**	The second 15-min block of the first half will begin.
**T20**	TC, PT and TS will be evaluated after the end of the second block.
**T21**	First “water break” is now going to occur. The third 15-min block of the first half will start.
**T22**	TC, PT and TS will be assessed after the end of the third block and half-time period is going to start.
**T23**	If needed, participants will towel-dry themselves and then have their body mass measured (before and after urine excretion) with the same scale and while wearing the same clothes as the pre-exercise body mass assessment. Water bottles will be weighted.
**T24**	The same beverage (as in T8) will be provided to each participant, exactly in same conditions as in the pre-cooling phase. The first 1/3 of the 75 ml of the same beverage will be administered.
**T25**	TC, PT and TS will be recorded.
**T26**	The second 1/3 of the 75 ml of per-cooling beverage will be distributed.
**T27**	TC, PT and TS will be evaluated.
**T28**	The third 1/3 of the 75 ml of per-cooling beverage will be administered.
**T29**	TC, PT and TS will be accessed.
**T30**	The first 15-min block of the second half will start.
**T31**	TC, PT and TS will be recorded again after the end of the fourth block.
**T32**	The second 15-min block of the second half will begin.
**T33**	TC, PT and TS will be evaluated after the end of the fifth block.
**T34**	Second “water break” will occur. The third 15-min block of the second half will start.
**T35**	TC, PT and TS will be evaluated at the end of the sixth block.
**T36**	Lactate and blood glucose levels are going to be reassessed.
**T37**	Participants will towel-dry themselves and then have their body mass measured (before urine excretion) with the same scale and while wearing the same clothes as the pre-exercise body mass assessment. Water bottles will be weighed. Subsequently, the difference between the referee's weight at T4 and T37 is going to be calculated, to estimate whole-body sweat loss as well as SR during the protocol (the volume of fluid intake is going to be subtracted, as well as urine output).
**T38**	Hydration status is going to be evaluated, after urine collection.
**T39**	RPE will be assessed.

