##### Sweating rate

2.4.6.2

SR is going to be calculated recurring to the following equation [36]:$$SR=\frac{Pre\;exercise\;body\;weight-postexercise\;body\;weight+fluid\;intake-urine\;volume}{exercise\;time\;in\;hours}$$

Pre-exercise body weight will be measured after participants voiding their bladder. Body weight will be measured on a digital platform scale (Seca, Hamburg, Germany), with minimal clothing, to the nearest 0.1 kg. Post-exercise body weight is going to be evaluated also with minimal clothing, after participants' towel-off themselves, at the half-time, before and after urine excretion (if needed), and at the end of the protocol. Fluid intake is going to be recorded via the measurement of mass change of the individual bottles, provided to the participants, at the warm-up and at the end of the first “water break” at the end of the session, to the nearest 0.1 ml (Seca, Hamburg, Germany). Urine volume will be determined through the difference of the referees' weight before and after urine excretion, using a digital platform scale. Participants will be advised not to rinse and spit out the fluids from the bottle at any time of the trial and that they should not drink any other beverages other than those provided by the researchers. Also, fluid intake will only be allowed in the 30th minute of each half, to simulate “cooling break” (“water break”) rule implemented by FIFA. FIFA's guidelines for extreme heat conditions (i.e. a WGBT of more than 32 °C) refer cooling breaks are mandatory in both halves of a match, around the 30th minute and 75th minute, so that football players and referees may rehydrate [37].

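### Step T37 of Table 1 subtracts fluid intake from the weight loss, whereas the sweating-rate equation in section 2.4.6.2 adds it; T37 should be reworded to match the equation

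*Protocol article*

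**What the plan says.** The Outcomes section (2.4.6) states that "Physiological primary outcomes include heart rate (HR), SR and Tcore".

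Section 2.4.6.2 introduces its formula with "SR is going to be calculated recurring to the following equation". The formula is pre-exercise weight minus post-exercise weight, plus fluid intake, minus urine volume, all divided by exercise time in hours. For the intake term, "Fluid intake is going to be recorded via the measurement of mass change of the individual bottles".

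Table 1 in section 2.4.7 covers the same calculation at step T37: "the difference between the referee's weight at T4 and T37 is going to be calculated, to estimate whole-body sweat loss as well as SR". A parenthesis in the same sentence adds that "the volume of fluid intake is going to be subtracted, as well as urine output".

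Table 1 also describes the intake measurement at step T4, where individual bottles are handed out so that fluid taken at the water breaks "may be recorded via the measurement of body mass changes". T23 and T37, however, both have the water bottles weighed.

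**The concern.** The two places give fluid intake opposite signs. The equation adds it; T37 subtracts it. Urine is subtracted in both. Only one rule can return sweat loss, and T37 sits in the step-by-step table that describes the trial day.

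A fixed error common to both sessions would drop out of a crossover comparison. This one scales with the amount each referee drinks, and that amount is not fixed: "Participants will be informed that they may drink water" freely at the breaks. If intake differed between the menthol and placebo sessions, T37 applied literally would turn that difference into an apparent SR difference of opposite sign, with no change in sweating.

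T4 is a smaller matter concerning the same quantity. It names body mass where section 2.4.6.2 names bottle mass.

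**Working it through.** **Inputs**

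- Weight difference D = body mass at T4 minus body mass at T37 (Table 1).
- Signs in the equation: intake plus, urine minus (section 2.4.6.2).
- Signs in T37: intake minus, urine minus (Table 1).
- Exercise time t: 1.5 h for the 90-min protocol. A value of 1.75 h, which counts the 15-min warm-up, is shown only as a sensitivity check.
- Fluid intake F: not given in the protocol. Range assumed here: 0.2 to 1.0 L.
- Sweat loss S: 1.60 L, used only as a scale. The Introduction reports this as the mean body water loss of referees in a match and does not say whether it is net or gross of drinking.
- Urine passed between the two weighings: U. 1 kg is taken as 1 L.

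**Mass balance**

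Between T4 and T37 a referee loses S and U and gains F, so D = S + U − F.

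- Section 2.4.6.2: D + F − U = (S + U − F) + F − U = **S**.
- T37 as worded: D − F − U = (S + U − F) − F − U = **S − 2F**.

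The gap is 2F in litres, or 2F/t in SR, whatever the values of S and U.

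**Can T37 be read another way?**

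Suppose that subtracted means taken off the post-exercise weight. The result is then D + F + U = S + 2U. Intake now has the right sign but urine has the wrong one. The equation gives the two terms opposite signs and T37 gives them the same sign, so no literal reading of T37 agrees with the equation unless F or U is zero.

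**Size of the error in SR (S = 1.60 L, U = 0, t = 1.5 h)**

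| Intake F | Equation | T37 | Error in SR |
|---|---|---|---|
| 0.2 L | 1.60/1.5 = 1.07 L/h | 1.20/1.5 = 0.80 L/h | −0.27 L/h |
| 0.5 L | 1.07 L/h | 0.60/1.5 = 0.40 L/h | −0.67 L/h |
| 1.0 L | 1.07 L/h | −0.40/1.5 = −0.27 L/h | −1.33 L/h |

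With t = 1.75 h the errors are −0.23, −0.57 and −1.14 L/h. The error column does not depend on the choice of S.

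**Effect on the comparison between conditions**

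If intake under menthol differs from placebo by ΔF, T37 adds −2ΔF/t to the SR difference. For a hypothetical ΔF of −0.1 L this is 2 × 0.1/1.5 = +0.13 L/h (+0.11 L/h at 1.75 h). For −0.2 L it is +0.27 L/h (+0.23 L/h). For ΔF = 0 it is zero.

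**T4**

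Table 1 schedules body mass at T4, T23 and T37. None of these weighings brackets the water breaks at T21 and T34, so body mass cannot isolate what was drunk there. Bottle mass can.

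**The case against.** The best defence is that the method is fixed in section 2.4.6.2 by a displayed, cited and correct equation, whereas T37 is a parenthesis in a timeline table. T37 gives no denominator, so nobody could compute SR from it alone and an analyst would have to return to the equation. The word subtracted may be loose drafting for corrected for. Body mass, bottle mass and urine are all recorded as raw values, so a wrong sign could be reversed without loss. The range and consistency checks in section 2.5 should also catch a negative sweating rate. In T4, body looks like a slip for bottle, since T23 and T37 both weigh the bottles.

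All of this stands, and it limits the consequence. It does not remove the conflict: T37 states a rule for a primary outcome that is wrong if followed, and nothing in the article says which text prevails. The consistency checks are also weak protection at low intake. With 0.2 L drunk, T37 gives 0.80 L/h in the example above, which is not an impossible value.

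A reader might go further and infer that menthol is expected to change how much the referees drink, so that a false SR effect is likely. The article does not support that. The Discussion says that menthol has been shown to reduce thirst, but no section predicts a difference in fluid intake. A difference is possible, and its size and direction are unknown.

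**Conclusion.** The inconsistency is real. The equation in section 2.4.6.2 satisfies mass balance and T37 does not. Followed literally, T37 understates sweat loss by exactly twice the fluid drunk, and SR by 2F/t. That algebra rests on no assumed figure. The sizes in L/h do: they assume an intake of 0.2 to 1.0 L, for which the protocol gives no value, and 1.5 h of exercise. The upper end may be high, because drinking is allowed only at two breaks, which the Discussion describes as lasting 1 min. The bias in the menthol-versus-placebo comparison is zero if intake is equal in both conditions and −2ΔF/t otherwise.

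One might infer that the trial's SR results will be wrong or that the data are compromised. The documents do not support this. The correct formula is in the article, the raw weights allow recalculation, and the sample size rests on thermal sensation (section 2.1), not on SR. Nor does the T4 wording show that intake cannot be measured, since bottle weighing is scheduled elsewhere in the same table. This is a wording correction to the calculation of one of several primary outcomes.

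**What to change.** - **T37:** replace the parenthesis with the rule of section 2.4.6.2, so that sweat loss = T4 mass − T37 mass + bottle-measured fluid intake − urine passed between T4 and T37. The T37 weight is taken before the final urine collection, so urine passed after that weighing does not enter.
- **T4 (side correction):** say that water-break intake is recorded by the mass change of the bottles, in line with section 2.4.6.2, T23 and T37.

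The cost is two wording changes in Table 1. No new measurement is needed, and neither the visit schedule nor the sample size changes.
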